#### Statistical analysis

Data will be analyzed on the intention-to-treat (ITT) principle. Missing data will not be replaced. Prior to analysis, the normality of the data will be checked by the Shapiro-Wilks test, and an attempt will be made to convert non-normally distributed variables into normally-distributed variables using appropriate variable transformations (logarithmic transformation, square root transformation, reciprocal transformation, power transformation). Descriptive statistics will be reported as mean ± standard deviation for continuous variables and as N (percent frequency) for discrete variables. Between-group comparisons will be carried out by one-way analysis of variance (ANOVA) and by the Chi-squared test for continuous and categorical variables respectively. A significant result from ANOVA will be followed up by post-hoc analysis (Tukey HSD). The effect of treatment over time for the variables under consideration will be investigated by a two-factor repeated measures ANOVA, the first factor being TREATMENT (between factor, three groups: digital-based cognitive rehabilitation combined with motor rehabilitation, paper-based cognitive rehabilitation combined with motor rehabilitation, motor training alone), and the second factor being TIME (within factor, three measurements: baseline, post-treatment, and follow-up), with repeated measurements in the time factor. Mauchly’s test of sphericity will be used to assess the sphericity assumption and the Greenhouse-Geisser correction will be applied if appropriate. A significant result from repeated measures ANOVA will be followed up by post-hoc analysis for pairwise comparisons (Dunn-Sidak).

Between group baseline homogeneity of potential confounding variables should be guaranteed by the randomization protocol, but it will be checked before analysis. In case of significant differences, analysis of covariance (ANCOVA) will be used, adjusting for covariates that may influence the outcome.

All statistical tests will be two-tailed and a p-value <0.05 will be considered statistically significant. All analyses will be carried out using the SAS/STAT statistical package, release 9.4 (SAS Institute Inc., Cary, NC, USA) by a biostatistician from the Biomedical Engineering Unit.

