#### Withdrawal

Patients having acute organic events or manifesting the need for pharmacological treatment during the training will be excluded from the study.

Participants who no longer wish to participate in the trial may withdraw at any time without further explanation. To perform intention-to-treat analyses with as little missing data as possible, the investigator may ask the participant to use data already collected and whenever possible, the participant will be asked for permission to obtain data for the primary outcome measure.

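### The repeated-measures ANOVA uses only patients seen at all three visits, which does not fit the stated intention-to-treat principle, and the protocol does not name the primary test for MMSE

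*Protocol article*

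**What the plan says.** Four statements in the Statistical analysis section of the protocol article bear on this point.

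- Principle: "Data will be analyzed on the intention-to-treat (ITT) principle".
- Missing values: "Missing data will not be replaced".
- Longitudinal test: "The effect of treatment over time for the variables under consideration will be investigated by a two-factor repeated measures ANOVA", with TIME as the "within factor, three measurements: baseline, post-treatment, and follow-up". Sphericity is checked by Mauchly's test, and "the Greenhouse-Geisser correction will be applied if appropriate".
- A second test: "Between-group comparisons will be carried out by one-way analysis of variance (ANOVA" for continuous variables), followed by Tukey comparisons.

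The Sample size section sizes the trial by one-way ANOVA on the MMSE change from enrolment to end of treatment. It needs 63 patients, raised to 75 for up to 16% drop-out. The Study timeline puts T2 three months after training ends. The Withdrawal section removes patients with certain events during training. For participants who withdraw, it seeks permission to obtain the primary outcome, with the aim "To perform intention-to-treat analyses with as little missing data as possible".

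**The concern.** Mauchly's test and the Greenhouse-Geisser correction mark the longitudinal test as the classical ANOVA rather than a likelihood-based mixed model. In its standard form the classical test needs a complete T0, T1 and T2 record for each patient. With no replacement of missing values, a patient who trained for 8 weeks and was measured at T1 leaves the test if the 3-month visit is missed.

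Two things are at stake. First, whether a patient attends T2 may depend on how that patient did at T1. The T1 information from this test then comes from a selected group, although the T1 values of the others were observed. Second, MMSE data retrieved after withdrawal contribute nothing to this test if the patient's set of three stays incomplete, which works against the purpose given in the Withdrawal section.

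This is not a detail left to an analysis plan. The article itself fixes both the model and the no-replacement rule.

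**Working it through.** **1. The plan's own sample size.** Inputs from the Sample size section: means 0, 0.7 and 1.4; SD 1.41; alpha 0.05; 80% power. The noncentrality is λ = n·Σ(μᵢ − μ̄)²/SD².

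- Σ(μᵢ − μ̄)² = 0.49 + 0 + 0.49 = 0.98, and SD² = 1.9881.
- n = 20 per arm: λ = 20 × 0.98/1.9881 = 9.86; F with 2 and 57 df; power 0.787.
- n = 21 per arm: λ = 10.35; 2 and 60 df; power 0.809.
- Inflation: 63/(1 − 0.16) = 75.

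Both stated figures reproduce. They belong to a two-visit change score.

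**2. Who enters each test, by values observed.**

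| MMSE observed | Repeated-measures ANOVA | One-way ANOVA on T1 − T0 | Mixed model, baseline as covariate |
|---|---|---|---|
| T0, T1, T2 | in | in | in |
| T0, T1 | out | in | in |
| T0, T2 | out | out | in |
| T0 only | out | out | no contribution |

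**3. Numbers analysed.** If total loss by T2 is 16%, the three-visit set is 75 × 0.84 = 63, as planned. The article does not say whether the 16% extends to T2. If 16% are lost by T1 and a further 5%, 10%, 15% or 20% of the rest miss T2 (assumed range), the set is 63 × 0.95, 0.90, 0.85 or 0.80, which is about 60, 57, 54 or 50.

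**4. Illustration of bias.** All inputs here except the arm means and the measurement error of 1 point are assumptions. Every patient attends T1. The change has SD √2 = 1.41 and arm means 0, 0.7 and 1.4, so the true digital-minus-motor difference is 1.40. The probability of missing T2 is 1/(1 + exp(−(a + b × T1 change))), with the same a and b in all arms unless stated. The intercept a is set to give the overall loss shown.

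| Mechanism | Loss at T2 | T1 difference in completers |
|---|---|---|
| Completely at random | 16% | 1.40 |
| b = −0.3 (a ≈ −1.6) | 15% | 1.37 |
| b = −0.7 (a ≈ −1.7) | 14% | 1.28 |
| b = −0.7 (a ≈ −1.0) | about 22% | 1.24 |
| b = −1.0 (a ≈ −0.8) | 26% | 1.13 |
| Digital arm only: logit = −2.05 − 1.0 × (change − 1.4); other arms random | 18% digital, 16% others | 1.68 |

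Using every observed T1 value gives 1.40 in each row, because here no T1 value is missing.

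**5. Scale.** The standard error of a two-arm difference at 21 per arm is 1.41 × √(2/21) = 0.44. The shifts run from −0.03 (1.37 − 1.40) through −0.27 (1.13 − 1.40) to +0.28 (1.68 − 1.40).

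**The case against.** The strongest reply is that the repeated-measures ANOVA is not the only test. The one-way ANOVA is named in the same section and was used for sizing on the T1 − T0 change. If it is the main MMSE test, a patient missing only T2 stays in the T1 comparison. This stands, and it limits the point. A reader might infer that the whole efficacy analysis is a completers analysis under an ITT label, or that missing T2 removes a patient from every T1 comparison. The document supports neither, because it does not say which test is primary. But the repeated-measures ANOVA is the only test expressly assigned to the effect of treatment over time, and the one-way test without replacement still omits anyone lacking T0 or T1.

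A reader might also infer that dropout favours the weaker arm. That follows only if dropout depends on T1 change in the same way in every arm. The arm-specific case goes the other way, and missing completely at random gives no bias. No dropout slope is stated in the document.

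Nor can it be said that the trial is underpowered. The allowance from 63 to 75 already treats drop-outs as not analysed. Powers of 76%, 72% and 65% can be computed for losses of 25%, 30% and 40%, but the document gives no such losses, and those powers belong to the one-way test, not to the treatment-by-time test.

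Finally, retrieving outcomes after withdrawal reduces missingness. It does so, but it does not change how the remaining gaps are handled.

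**Conclusion.** The point holds for the repeated-measures ANOVA. As specified, it analyses only patients with complete T0, T1 and T2 data. This conflicts with the stated intention-to-treat principle and sets aside observed T1 MMSE values, including retrieved ones when the patient's set stays incomplete. The choice of primary MMSE test is left open, and that choice decides how far T2 loss reaches into the T1 result.

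The effect on the estimate cannot be known from the document. Under the assumed mechanisms it runs from nil to about 0.3 MMSE points in either direction, against a true difference of 1.40 and a standard error of about 0.44. At the planned 16% loss the T1 change test has its planned 81% power. Only total loss above 16% by T2 takes the three-visit set below 63. The sample size for T1 is arithmetically right. This should be fixed before analysis, but it does not invalidate the trial.

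**What to change.** For MMSE, replace the repeated-measures ANOVA by a likelihood-based mixed model for repeated measures:

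- outcome: MMSE at T1 and T2;
- fixed effects: treatment, visit, treatment × visit and baseline MMSE;
- covariance: unstructured;
- data: all observed post-baseline values of all randomised patients.

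Name the T1 treatment contrast, on which the trial was sized, as the primary comparison. Drop the Mauchly and Greenhouse-Geisser step, which the unstructured covariance makes unnecessary.

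Patients with no post-baseline MMSE still do not contribute to this model, so it does not by itself meet the intention-to-treat aim in full. Add one sensitivity analysis for data missing not at random, for example a delta adjustment.

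The cost is revised wording and a little more analysis work, with no new data. The software need not change: "All analyses will be carried out using the SAS/STAT statistical package, release 9.4", and that package fits such models. The downside is reliance on missing at random, which the sensitivity analysis is there to probe.

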### Data analysis

#### Sample size

The sample size was calculated considering the MMSE score, the primary outcome of the trial. We required the sample size to be large enough to detect a difference in efficacy (measured as MMSE at the end of treatment—MMSE at enrolment) of 1.4 MMSE points between the most effective treatment and the least effective treatment. This value was selected because it is reported in literature as the lowest threshold for the minimum clinically important difference (MCID) [39,53]. To be conservative, the third treatment was assumed to be as effective as the average of the other two. The aim was to detect this difference with a two-sided type I error of 5% and 80% power. From previous studies in populations similar to ours [54], the standard error of measurement (SEM) for the MMSE is 1 point, giving an SD of 1.41 (resulting in a Cohen’s effect size close to 1). The sample size was then estimated at 63 patients (21 per group). Taking into account the possibility of losing some patients (up to 16% of drop-outs), the required sample size was set at 75 patients (25 per group). Computations were performed using the ’proc power’ of the SAS statistical package with the following parameters: one-way ANOVA as statistical model, 0, 0.7 and 1.4 as group means, 1.41 as standard deviation, 0.05 as alpha and 0.8 as power (SAS/STAT, release 9.4, SA Institute Inc., Cary, NC, USA).

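### The 80% power belongs to a one-way ANOVA of T1–T0 MMSE change, but the analysis section lists two omnibus procedures and does not say which decides the primary endpoint, and its repeated-measures post-hoc trigger names no effect

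*Protocol article*

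**What the plan says.** The Sample size section defines efficacy as a change score, "measured as MMSE at the end of treatment—MMSE at enrolment", and gives the SAS inputs as "one-way ANOVA as statistical model, 0, 0.7 and 1.4 as group means, 1.41 as standard deviation, 0.05 as alpha and 0.8 as power". The target is a difference "of 1.4 MMSE points between the most effective treatment and the least effective treatment". The error rates are stated as "The aim was to detect this difference with a two-sided type I error of 5% and 80% power", and the result as "The sample size was then estimated at 63 patients (21 per group"), raised to 75 for up to 16% drop-out.

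The Statistical analysis section sets out two routes:

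- One-way ANOVA for between-group comparisons of continuous variables, with Tukey HSD after a significant result. No variable, visit or change score is named.
- A two-factor repeated-measures ANOVA for the effect of treatment over time, with TREATMENT (three groups) and TIME (baseline, post-treatment, follow-up). Of this it says "A significant result from repeated measures ANOVA will be followed up by post-hoc analysis for pairwise comparisons (Dunn-Sidak").

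Every test is two-tailed at p<0.05. The Primary outcome measure and Study end-point sections name the MMSE but give neither a deciding test nor a deciding visit.

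**The concern.** The repeated-measures model produces three F tests, which answer different questions:

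- TREATMENT compares arm means averaged over all three visits. One of these is the pre-treatment baseline, where randomised arms do not differ in expectation, so the effect is diluted.
- TIME asks whether the MMSE moves over the study in all arms together. Practice or common improvement is enough to make it significant, and it says nothing about the difference between arms.
- TREATMENT × TIME (4 df) combines the effect at 8 weeks with its persistence three months after training ends.

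None of these is the 2-df comparison of T1–T0 change used for sizing. With no designated primary test, the reader of the final report cannot tell which result was meant to carry the claim. The stated power describes only one of the candidates, and the 5% level holds test by test rather than for the primary conclusion. Because the trigger names no effect, a TIME effect alone would license pairwise comparisons.

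**Working it through.** **Inputs from the Sample size section.** Three groups; mean changes 0, 0.7 and 1.4; SD of change 1.41, from "the standard error of measurement (SEM) for the MMSE is 1 point, giving an SD of 1.41"; alpha 0.05; n = 21 per group.

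**Assumptions not in the document.** Sphericity (compound symmetry); between-patient SD σ_b of 1 to 3 MMSE points; a T2 effect fully kept, halved or fully lost. The within-patient error variance is set so that the change SD is 1.41: σ_e² = 1.41²/2 = 0.994.

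**1. The plan's own figure.** λ = n·Σ(μ_i − μ̄)²/SD² = 21 × 0.98/1.988 = 10.35. With 2 and 60 df the power is 0.809; at n = 20 it is 0.787. So 21 per group (63 in all) reproduces, and 63/(1 − 0.16) = 75. The stated 80% is correct for the one-way ANOVA of T1–T0 change.

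**2. TREATMENT × TIME (4 and 120 df).** λ = n·Σ(interaction terms)²/σ_e². This does not depend on σ_b.

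| T2 effect | Σ(interaction terms)² | λ | Power |
|---|---|---|---|
| kept | 0.653 | 21 × 0.653/0.994 = 13.8 | 0.845 |
| halved | 0.490 | 21 × 0.490/0.994 = 10.35 | 0.714 |
| lost | 0.653 | 13.8 | 0.845 |

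In the halved case λ is the same as in step 1, but it is spread over 4 df instead of 2, so power falls.

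**3. TREATMENT main effect (2 and 60 df).** The best-to-worst difference averaged over three visits is (0 + 1.4 + 1.4)/3 = 0.93 if kept, (0 + 1.4 + 0.7)/3 = 0.70 if halved, and (0 + 1.4 + 0)/3 = 0.47 if lost. The variance of a patient's mean is σ_b² + 0.994/3.

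| T2 effect | σ_b = 1 | σ_b = 2 | σ_b = 3 |
|---|---|---|---|
| kept | 0.62 | 0.23 | 0.13 |
| halved | 0.39 | 0.14 | 0.09 |
| lost | 0.19 | 0.09 | 0.07 |

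**4. False positives with no arm difference (simulation, n = 21 per arm).** Each F test alone rejects in about 5% of trials. The change ANOVA or the interaction rejects in about 7.5%; the two are correlated, so this is below 1 − 0.95² = 9.75%. The TREATMENT main effect rests on patient means, which are independent of the within-patient contrasts. Adding it gives 1 − 0.925 × 0.95 = 0.121, and simulation also gives about 12%.

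**5. TIME as a trigger.** Suppose all arms gain 0.7 points at T1 and hold it at T2. Then λ = 63 × (0.7² × 2/3)/0.994 = 20.7, and TIME is significant in about 98.6% of trials. With a common gain of 1.4 points it is significant in essentially all of them. Under that 1.4-point gain with no arm difference, some between-arm pair at some visit is falsely significant in about 8–11% of trials if Dunn-Sidak covers three pairs per visit, and in about 3–4% if it covers all nine.

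**The case against.** The strongest reply is that the powered test may well be in the plan. One-way ANOVA is listed for continuous variables, and MMSE change is one. The stated purpose of the repeated-measures model, treatment over time, points to the interaction. The exact Sidak family and model contrasts are details that a condensed article may leave to a fuller document. Each F test is valid at 5%.

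Much of this stands, and it rules out several stronger readings that a reader might infer:

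- That the sizing test is absent from the analysis. The text does not show this; it shows that the test is not designated as primary.
- That the 5% level is wrong for the planned tests. Each F test holds its level; the excess arises only if more than one may carry the claim.
- That the trial is underpowered. Interaction power matches or exceeds the stated 80% in two of the three T2 patterns and falls short only with partial waning.
- That the low TREATMENT main-effect power is the trial's power. The protocol does not say that this effect will be read as efficacy, and the range rests on an unstated between-patient SD. The 12% figure carries the same condition.
- That pairwise error necessarily exceeds 5%. This depends on the Dunn-Sidak family, which is not given.

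The reply does not remove the defect. The section does state its procedures, and as stated there are two omnibus routes, two post-hoc methods and a trigger that any of three effects can meet. This is a rule fixed ambiguously, not merely a detail left out.

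**Conclusion.** The point holds in this form: power and alpha are computed for one test, and the analysis section does not make that test the primary one.

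The size depends on which test is used. Power is 81% for T1–T0 change. For the interaction it is about 84–85% if the T2 effect is fully kept or lost and about 71% if halved. For the baseline-averaged TREATMENT effect it is about 7–62%. The chance of a false claim is about 7.5% if either the change ANOVA or the interaction may carry it, and about 12% if the TREATMENT main effect may as well.

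The interaction figures rest on sphericity and the assumed T2 pattern; the main-effect figures also rest on σ_b of 1 to 3. That TIME alone satisfies the trigger follows from the wording and needs no assumption about σ_b. This should be corrected, but it does not invalidate the sample size.

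**What to change.** Before outcome data are seen by arm, state:

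1. **Primary test:** the 2-df treatment comparison of MMSE at T1 (8 weeks), adjusted for baseline MMSE, at two-sided 5%. It is followed, if significant, only by the three treatment pairs at T1, with one named post-hoc procedure.
2. **Secondary:** the repeated-measures model and the T2 comparison, with TREATMENT × TIME as the only effect that opens post-hoc tests, and the family of pairs defined.
3. **Not evidence of efficacy:** the TIME main effect and the baseline-averaged TREATMENT main effect. Neither triggers comparisons between arms.

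Naming the unadjusted T1–T0 change ANOVA as primary would also remove the ambiguity. Baseline adjustment is preferable because, with equal variances at the two visits and correlation ρ, its residual variance is (1 + ρ)/2 times that of the change score, so the 63 evaluable patients remain sufficient on the plan's own inputs. If the sponsor prefers the interaction as primary, power should be recomputed for it with a stated T2 effect.

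The cost is wording only: no change to sample size, visits or data collected.

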### Outcome measures

#### Primary outcome measure

The primary measure implemented for the present study will be the MMSE (normed total) [39].

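### Covariate adjustment is triggered by a significance test of baseline balance; adjusting for baseline MMSE in every case would be more precise and cost one degree of freedom

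*Protocol article*

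**What the plan says.** All of this is in the protocol article, under Data analysis.

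- **Default comparison** (Statistical analysis): "Between-group comparisons will be carried out by one-way analysis of variance (ANOVA) and by the Chi-squared test for continuous and categorical variables respectively". No covariate is included.
- **Longitudinal analysis** (Statistical analysis): a treatment-by-time repeated-measures ANOVA with TIME as a "within factor, three measurements: baseline, post-treatment, and follow-up". Baseline is therefore one of the responses, not a covariate.
- **Baseline check** (Statistical analysis): homogeneity of potential confounders "should be guaranteed by the randomization protocol, but it will be checked before analysis".
- **Trigger** (Statistical analysis): "In case of significant differences, analysis of covariance (ANCOVA) will be used, adjusting for covariates that may influence the outcome". The same section sets two-tailed p<0.05 as the threshold for all tests.
- **Effect measure** (Sample size): the difference between MMSE at the end of treatment and at enrolment. The design parameters for the one-way ANOVA are "0, 0.7 and 1.4 as group means, 1.41 as standard deviation, 0.05 as alpha and 0.8 as power".

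No section makes baseline MMSE a fixed covariate.

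**The concern.** The rule lets a significance test on the trial's own baseline data choose the model. After proper randomisation, any baseline difference is due to chance, so the test cannot show that something needs repair. What makes a covariate worth adjusting for is how strongly it predicts the outcome. Baseline MMSE can be expected to predict later MMSE whether or not the arms happen to differ.

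Two things are at stake. The first is precision: a change score uses baseline with a fixed slope of 1, whereas ANCOVA estimates the slope and has smaller residual variance whenever the correlation is below 1. The second is chance imbalance. An arm that starts lower tends to gain more through regression to the mean, and the rule leaves this uncorrected in every trial where the imbalance falls short of p<0.05.

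**Working it through.** **Inputs from the protocol (Sample size; Statistical analysis).** Group means 0, 0.7 and 1.4; change SD 1.41; alpha 0.05; 21 evaluable and 25 enrolled per group; 16% drop-out.

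**Assumed, because the protocol does not give it.** The baseline-to-post correlation of MMSE, rho, shown from 0.5 to 0.9. Variances at the two visits are taken as equal.

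**1. The plan's own figure.** The noncentrality of the three-group F test is 21 × (0.7² + 0² + 0.7²) / 1.41² = 20.58 / 1.988 = 10.35. With 2 and 60 df, power is 80.9%; at 20 per group it is 78.7%. So 21 per group (63) is reproduced, and 63 / 0.84 = 75 enrolled.

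**2. Always adjusting for baseline MMSE.** The residual variance of ANCOVA relative to a change score is (1 + rho)/2, and one error df is lost (59 instead of 60). The change SD is held at 1.41.

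| rho | variance ratio | noncentrality | power at 21 per group | n per group for 80% |
|---|---|---|---|---|
| 0.5 | 0.75 | 13.80 | 91.0% | 16 |
| 0.7 | 0.85 | 12.18 | 87.1% | 18 |
| 0.8 | 0.90 | 11.50 | 85.0% | 19 |
| 0.9 | 0.95 | 10.90 | 82.9% | 20 |

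**3. The conditional rule, simulated.** There were 100,000 trials per scenario at 21 per group. Baseline MMSE is tested by ANOVA; ANCOVA is used if p<0.05, otherwise change-score ANOVA.

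| rho | power, conditional rule | power, ANCOVA always | null rejection, conditional rule |
|---|---|---|---|
| 0.5 | 81.6% | 90.7% | 4.3% |
| 0.7 | 81.2% | 86.6% | 4.6% |
| 0.89 | 80.7% | 82.3% | 4.8% |

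The rule switches to ANCOVA in only about 5% of trials, which is why it recovers so little. Simulated ANCOVA power is slightly below step 2 because the formula ignores the small cost of chance baseline differences.

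**4. Error rates given an imbalance.** Under the null, in the roughly 5% of trials with a significant baseline MMSE difference, an unadjusted change analysis would reject in 16.0%, 11.8% and 7.6% at rho 0.5, 0.7 and 0.89; ANCOVA rejects in about 5%. The rule does switch to ANCOVA in these trials. That explains the slightly low overall rate: at rho 0.5, 4.87% − 4.99% × (15.98% − 4.81%) = 4.3%.

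**5. Imbalance that the test does not flag.** A 0.5 SD baseline difference between two arms of 25 gives t = 0.5 × √(25/2) = 1.77 on 48 df, p = 0.083. In the three-arm ANOVA with the third arm midway, F = [25 × (0.25² + 0.25²)] / 2 = 1.56 on 2 and 72 df, p = 0.22.

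Such a difference shifts the expected difference in change by (1 − rho) × 0.5 × baseline SD. Holding the change SD at 1.41 fixes the baseline SD at 1.41 / √(2(1 − rho)).

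| rho | implied baseline SD | shift (points) | share of 1.4 |
|---|---|---|---|
| 0.5 | 1.41 | 0.35 | 25% |
| 0.7 | 1.82 | 0.27 | 20% |
| 0.8 | 2.23 | 0.22 | 16% |
| 0.89 | 3.01 | 0.17 | 12% |

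**The case against.** The plan does not ignore baseline. Efficacy is defined as change from enrolment, and the repeated-measures model includes baseline as a time level. The trial was sized for a change-score ANOVA and meets its power target on its own inputs. The gain from ANCOVA also shrinks as rho rises: if baseline MMSE had an SD of about 3, the plan's change SD of 1.41 would imply rho of about 0.89, and the simulated gain over the conditional rule is then under two percentage points. All of this stands, and it limits the size of the point. It does not justify the trigger, which has no advantage over fixed adjustment.

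Three stronger readings are tempting but not supported.

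- **Inflated false positives.** A reader might infer this from a data-dependent model choice. With baseline MMSE as the covariate, the rule is slightly conservative overall.
- **A model chosen with results in view.** The protocol places the homogeneity check before analysis, and Participants randomization keeps the analysing biostatistician unaware of which code is which treatment. The choice depends on baseline data; nothing says that outcomes are seen first.
- **Unnamed covariates as a defect.** A journal article commonly leaves such a list to the full protocol or analysis plan, which is not shown. Adjusting for CDR or centre as well would be a preference, not something this text requires.

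**Conclusion.** The concern holds as a poorly chosen decision rule that the protocol states outright. Its cost is forgone precision and uncorrected chance imbalance, not a wrong sample size. Always adjusting would raise power from about 81% to between 83% (rho 0.9) and 91% (rho 0.5). An unflagged half-SD imbalance would shift the comparison of two arms by 0.17 to 0.35 points.

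These figures rest on the plan's change SD of 1.41, equal variances at the two visits and the assumed range of rho. A larger shift could be obtained by pairing a baseline SD of 3 with rho 0.7: 0.3 × 0.5 × 3 = 0.45 points. That pairing implies a change SD of 3 × √(2 × 0.3) = 2.32, which contradicts the plan's 1.41, so the figure should not be set beside the power results above.

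**What to change.** In Statistical analysis:

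- Make the primary analysis an ANCOVA of MMSE at the end of treatment (T1), with treatment group as factor and baseline MMSE as covariate, whatever any baseline comparison shows.
- Apply the same rule to each secondary outcome that has a baseline value, using that outcome's own baseline.
- Delete the significance-triggered ANCOVA rule and report baseline characteristics descriptively by arm, without tests.

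The cost is a change of wording and one error degree of freedom. Baseline MMSE is already collected at T0, and the planned 63 evaluable and 75 enrolled patients remain sufficient.
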